# Data Analysis

*Intervention patterns of use – website analytics*

Data on intervention use and patterns of use will be collected by Cloud Data Service, the company that built the LEAP intervention, using website analytics systems such as Google Analytics. Usage metrics will be compared directly and over time to looks for patterns and trends in the data.

*Statistical analysis of data collected*

Statistical advice and support will be provided by [name] group from the School of Mathematics and Statistics, Newcastle University.

# Qualitative Assessment

*Objectives*: To conduct qualitative interviews with a purposive sample of participants invited to participate in the pilot trial, to explore reasons for participation or non-participation, experiences of using the intervention, and acceptability of the intervention and assessments

These data will help evaluate the feasibility of a future definitive RCT and explore: opportunities to maximise recruitment and retention; acceptability of data collection including use of the HAP assessment; use of the LEAP intervention including problems of accessibility and function when used within the home or work environment; and data on the acceptability and reported use of each module (diet, PA, social, changing work and time).

## Research Questions addressed by the Qualitative Interviews

With regard to qualitative outcomes in the pilot study, there are three overlapping domains of enquiry: 1) questions relating to participation in the pilot study; 2) questions relating to use of the intervention website; and 3) questions relating to the use of the HAP subset of measurement tools:

### Domain 1: Participation in pilot

1. How did those participating in the pilot come to be recruited? (what did they think about the recruitment strategy, materials etc.)
2. What are the reasons for refusing to participate? (small sub-sample)
3. Why do people agree to take part in the study?
4. What do participants expect from the study? (Are their expectations met?)
5. What are the reasons for trial retention?
6. What are the reasons for trial attrition? (small sub-sample)
7. How do participants feel about being randomised to their arm of the trial (compare and contrast the different conditions)?
8. What are participants’ experiences of the diet, PA and social measures assessment at each time point? (e.g. acceptable? time needed to complete? ease of completion? etc)

Our research questions point to recruitment from 4 groups: 2 arms of the trial, participants who decline to take part in the pilot (e.g. decline to be randomised to a trial arm) but consent to the qualitative component, and participants who drop out of the pilot before the final assessment but consent to a qualitative follow up interview).

### Domain 2: Acceptability and use of intervention tools

1. What do participants expect from the intervention website? (Are their expectations met?)
2. What are the reasons for using some modules and tools but not others?
3. What is useful about each module and tool, and what is not useful? (what could be improved?)
4. How do participants’ experience receiving and responding to notifications and prompts?
5. How do participants’ experience the mentor component of the website?
6. How do participants’ experience the website overall? (i.e., engaging, fun, boring, easy to use, intuitive, innovative etc.?)
7. What do participants anticipate will happen after the pilot study (regarding their behaviours, lifestyle and retirement trajectory?)

### Domain 3: Acceptability and use of HAP battery

1. How do participants’ experience the HAP assessment overall (e.g. time taken, impression of question type, format and delivery)?
2. What components/instruments of the HAP measures were acceptable, and which were difficult to complete (e.g. difficult to understand, repetitive, or ‘simplistic’)?
3. What (if anything) is missing from the HAP in terms of measuring health and wellbeing *in the retirement transition*?

## Recruitment and sampling

Semi-structured interviews will be conducted with a sample of participants in the trial from the intervention and control groups and two ‘reduced participation’ groups. The reduced participation groups will include people who initially declined to participate in the trial or to be randomised, but consented to a brief qualitative interview (n= up to 2), and people who withdraw from the trial but consent to a follow-up qualitative interview (n= up to 2), The number of participants interviewed from each group within the pilot trial is shown in Figure 3. In total therefore up to 28 participants will be included in the qualitative component of the pilot study, although the length of interview will vary by trial arm ranging from 60 to 20 minutes per interview. Interviews in the reduced participation groups may be considerably shorter (e.g. 10 minutes) in some instances.

|  | LEAP | Control | Reduced Participation |
| --- | --- | --- | --- |
| Participation stage: near baseline | (n≤ 8) | (n≤ 4) | Prior to randomisation: (n≤ 2) |
| Participation stage: near final assessment | (n≤ 8) | (n≤ 4) | Post randomisation: (n≤ 2) |
| Total: (n≤28) | **(n≤ 16)** | **(n≤ 8)** | **(n≤ 4)** |

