# STUDY DESIGN

This study is a pilot, individual randomised, single blinded, controlled trial of a web-based lifestyle intervention for people in the retirement transition versus a minimal intervention comparator. Embedded in the trial design is a qualitative process evaluation and an assessment of feasibility and acceptability of a battery of HAP outcome measures.

A total of **90** participants will be recruited and participants will be randomly allocated to one of two conditions:

1. LEAP intervention
2. Minimal intervention control comparator

An allocation ratio of 2:1 will be used for the intervention group compared to the control comparator group.

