6. In the next five days, the trial administrator will telephone each eligible participant to answer any questions and to ascertain whether they would like to accept the invitation to participate. If there are any questions that can’t be answered over the phone by the administrator, a date for follow-up correspondence (either by e-mail or phone according to the preference of the potential participant) will be made. The administrator will request an answer to the question from the relevant trial team personnel, and will then relay this information to the participant during the arranged follow-up correspondence. On verbal consent, the trial administrator will ask that the participant sign the consent form and keep it until one of the research team visits them. The administrator will then schedule an appointment at a convenient time when one of the study team will visit the participant at their home or place of work to obtain the signed informed consent form and conduct the baseline assessment. The researcher will attend the appointment with spare consent forms in case the participant mislaid their original consent form.
7. Baseline assessment visit - after receiving informed consent, a member of the study team will administer the HAP battery assessment as per protocol (Appendix A). The activity monitor device will be attached to the participant, and it will be explained that the device is to be worn continuously for the next 7 days. The participant will be provided with a prepaid stamped address envelope to return the device after 7 days. The 24 hour recall dietary assessment tool procedure will be explained and participant will complete the first of three days to be recorded, and a web link to the social relationships tools will be provided. During this assessment session participants will be asked to provide information on smoking, alcohol consumption and demographic (Attachment 4 – Baseline data form).
8. The trial administrator will be informed by the member of the study team when baseline assessment is complete and the administrator will randomise the participant to one of the trial conditions recording key information (e.g. name, D.O.B. and assigned identification number) into a central database. A pedometer and instructions for its use will be posted to participants allocated to receive the LEAP intervention. The trial administrator will telephone or email the participant a few days later to check that the pedometer was received.

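### Why people refuse is to be learned from at most two self-selected decliners, although the protocol already telephones every eligible person and could log a reason there

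*Protocol*

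**What the plan says.** Under Domain 1 of the Qualitative Assessment, question 2 is "What are the reasons for refusing to participate? (small sub-sample") and question 6 is "What are the reasons for trial attrition? (small sub-sample"). The section gives finding "opportunities to maximise recruitment and retention" as one use of the data.

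Recruitment and sampling, with the Figure 3 table, sets the size of the two reduced-participation groups. Before randomisation these are "people who initially declined to participate in the trial or to be randomised, but consented to a brief qualitative interview (n= up to 2"). After it they are "people who withdraw from the trial but consent to a follow-up qualitative interview (n= up to 2"). In all, "up to 28 participants will be included in the qualitative component of the pilot study".

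In the STUDY Procedure, step 6 has the administrator make a call within five days. The administrator "will telephone each eligible participant to answer any questions and to ascertain whether they would like to accept the invitation to participate". Steps 12 and 13 are the only steps that book interviews, and they book them only with LEAP participants (6 to 8 each time) and control participants (up to 4 each time). The quantitative questions under Recruitment and retention ask for rates and sample characteristics, not reasons.

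**The concern.** A pilot that is to inform recruitment for a definitive trial needs to know which reasons for refusal are frequent enough to act on. Here the described source is two people at most. They select themselves twice, first by declining the trial and then by agreeing to talk to the same team about it. Such people may well differ from those who simply say no.

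The moment at which a refusal is voiced is already in the procedure, because step 6 exists to obtain the yes or no. If nobody writes down the reason on that call, it cannot be recovered at the analysis stage. This is therefore a data-collection matter and not one for a statistical analysis plan.

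The same thinness affects reasons for leaving. Two withdrawers across both arms say little about whether people leave LEAP and control for different reasons. The existing contacts are less useful there, so the remedy is weaker.

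**Working it through.** **1. The plan's own figure.** From the Figure 3 table: LEAP 8 + 8 = 16, control 4 + 4 = 8, reduced participation 2 + 2 = 4. The total is 16 + 8 + 4 = 28, as stated. The cap of two decliners and two withdrawers is therefore deliberate and internally consistent.

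**2. Is there another source of reasons in the text?** Reading steps 1 to 14 in order:
- Step 4 screens for eligibility by telephone.
- Step 6 calls every eligible person and learns whether they accept. No reason is mentioned.
- Steps 12 and 13 contact enrolled participants and book interviews with LEAP and control participants.
- No step invites a decliner or a withdrawer.

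The Sampling procedure draws from trial participants. It names qualitative-only consent and incomplete participation only as anticipated scenarios.

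**3. Share of decliners covered by two interviews.** Recruitment of 90 comes from STUDY DESIGN. The acceptance rate r is an assumption, because none is given. Decliners = 90/r − 90, and coverage = 2/decliners.

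| Assumed acceptance | Eligible | Decliners | Covered by 2 |
|---|---|---|---|
| 30% | 300 | 210 | 1% |
| 50% | 180 | 90 | 2% |
| 70% | 129 | 39 | 5% |
| 90% | 100 | 10 | 20% |

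**4. Share of leavers covered.** Attrition is also an assumption. Leavers = 90 × rate.

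| Assumed attrition | Leavers | Covered by 2 |
|---|---|---|
| 5% | 4.5 | 44% |
| 10% | 9 | 22% |
| 20% | 18 | 11% |
| 30% | 27 | 7% |

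**5. What two interviews can miss (illustration only).** If the two were random draws, a reason held by a share p of the group would go unheard with probability (1 − p)². For p = 10%, 25% and 50% this is 0.81, 0.56 and 0.25. Drawing without replacement from groups of 9 to 210 gives 0.54 to 0.60 for a reason held by about 25%. The interviewees are not random draws, so these figures indicate scale and are not estimates.

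**6. What the log would gain.** It would cover every decliner who is reached and answers. Even if only half gave a reason, the assumed 10 to 210 decliners would yield 5 to 105 reasons (10/2 to 210/2), against at most two.

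**The case against.** The case against is substantial, and most of it limits the point without removing it.

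- **Absence holds for the readable text only.** Figure 1 (the CONSORT flow) and Figure 2 (the administrative steps) are not shown, and either could carry a reasons box or a branch for decliners. A reader might infer that the trial records no reasons at all. The documents do not support that.
- **The small sub-sample is declared, and small numbers are normal for depth interviews.** Decliners and drop-outs are named as interview groups, with numbers, interview lengths and their own guides in Appendices D and E. It would be wrong to say that they are unprovided for or that two interviews are inadmissible. What is unstated is who invites them, and that nothing else feeds the question.
- **The recruitment and retention aim does not rest on four people.** Up to 24 interviews with enrolled participants also bear on it. Up to 12 of these are late ones (8 LEAP, 4 control), whose guides in Appendices B and C ask what helped people stay and what tempted them to leave. That speaks to retention in both arms. It does not speak to refusal, because everyone interviewed there had accepted.
- **The six-week call is a poor place to collect reasons for leaving.** The protocol itself expects most attrition within the first month, and step 13 books a follow-up visit that an earlier leaver will not need. The step 12 contact may be by email. A reader might infer that existing calls reach everyone who leaves. They do not.
- **Which reasons are common goes beyond the literal question.** Question 2 asks only what the reasons are. But acting on the answer to improve recruitment requires some idea of frequency.

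**Conclusion.** The point stands in a limited form. On the readable text, the question of why people refuse has one described source: at most two consenting decliners. No step invites them or records a reason, although a call to every eligible person is already planned. Under assumed acceptance of 30% to 90%, two interviews cover about 1% to 20% of decliners. They can illustrate reasons but cannot rank them.

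For attrition the same cap applies, but the late interviews partly compensate and no existing call reliably reaches those who have left, so less can be gained.

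The coverage figures rest on acceptance and attrition rates that the protocol does not state, and the conclusion about absence is subject to the two figures not shown. Severity is minor: the pilot remains valid, and one of its stated questions could be answered much better at little cost.

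**What to change.** First check Figures 1 and 2 for an existing reasons box or an invitation branch. If there is none:

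- **Step 6.** Ask each person who declines for one main reason. Make it voluntary, with a short list plus an option for other or not given. Log it without identifiers, since decliners have not signed consent and study codes are allocated only at consent. Offer the brief interview on the same call.
- **Domain 1, question 2.** State that the tabulated reasons are the main answer, with the number who gave none, and that the up to two interviews add depth.
- **Domain 1, question 6.** Whenever a participant tells the team that they are withdrawing, record a voluntary reason by study ID and join it to arm at analysis. This leaves the blinding of the follow-up assessors untouched. State that it covers only those who make contact.

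The cost is one field in the call log, a line or two in the procedure and about a minute per call. A sentence of ethics or information-sheet wording may be needed for decliners. Response will be incomplete, so the table should be read as coverage of those who answered, not of all who refused or left.

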**Fig 3. Diagram of the number of participants to be interviewed from each intervention group**

## Sampling procedure

The research questions cited above form the basis for our recruitment criteria. We will purposively sample from participants in the trial, aiming to achieve maximum variation with respect to our primary criteria outlined below.

Primary criteria: recruitment pathway (assuming assessment of different recruitment strategies); trial arm (2x conditions); gender; retirement stage (pre-retirement, partly retired, retired), occupation type (manual/non manual), socio-economic status.

Secondary criteria will shape sampling as the analysis develops (e.g. if gaps are identified in our qualitative dataset). Whilst it is not possible to identify these criteria at the outset, we anticipate that it will be necessary to recruit some participants in the following scenarios: module focus (e.g. if very few participants use a particular module, we will select those that do use the module to understand its attractiveness and function and the conditions which make it useful); participation level (fully participate, consent to qualitative study only, or incomplete participation).

## Data collection and analysis

Qualitative data will be collected through individual semi-structured interviews which will take place at the participants’ home or at a nearby location suitable for them. The scope and depth of the interviews will vary across groups. Participants drawn from the groups receiving the LEAP intervention will take part in an interview lasting up to 60 minutes. The interview schedule for this group is presented in Appendix B. Participants in the control condition will take part in an interview of up to 40 minutes duration. The interview schedule for this group is presented in Appendix C. Participants who initially declined to take part in the pilot, or those who withdrew from the pilot will take part in a brief interview of up to 20 minutes duration. Interview schedules for these groups are presented in Appendices D and E respectively.

We will conduct a thematic analysis (Guest etal., 2012) of the data using a coding manual developed by two of the research team (SM, BH) through preliminary analysis of data and the research questions and objectives. Data will be organised using a software package (NVivo).

## Anticipated time requirements

### Data collection

We anticipate approximately 6- 8 weeks for data collection (assuming all participants are already recruited to the trial and 4 interviews can be completed per week). In practice participants may take part in an qualitative interview on a rolling basis, following recruitment to the pilot study.

### Analysis

We estimate approximately 1 day to code a transcript (60-90 minute) using a basic coding frame. Therefore it will take approximately 6 weeks to initially code transcripts. It is difficult to estimate the time needed for analysis but for the purposes of writing a basic report we estimate approximately 5-6 weeks.

The total time to conduct the qualitative component of the pilot study therefore may take approximately 20 weeks.

# Data handling and record keeping

We will ask participants to read an information sheet about the study (Attachment 2 – Information sheet) and sign a consent form (Attachment 8 – consent form) prior to being recruited to the study.

Qualitative interviews (n=28) will be audio-recorded with respondents consent, and the recordings transcribed verbatim by an external transcription agency which have signed confidentiality agreements with Newcastle University. The single member of staff at the agency may be able to identify place and personal names from the audio-recordings. The transcripts will be anonymised during the process of transcription and will constitute data for analysis.

## Data Management

In line with good governance we will retain all primary data sources (audio recordings) for ten years so that they are available for re-analysis and audit should this requirement arise. Transcripts and audio recordings will be kept on a password protected secured server, accessible only to the research team throughout the duration of the LiveWell programme (current to 02/2015). Demographic information sheets and consent forms will be stored on university premises in a locked cabinet.

Permission for data sharing with third parties at the end of the study will be sought from all participants. All data to be shared will be rendered anonymous, and will be marked with a unique study identifier. For the first 24 months after the end of the LiveWell programme, the data will only be available to members of the LiveWell team (while further papers are being prepared for publication). Formal application and registration to use the data will be required. Anonymised transcripts of qualitative interviews will be offered in electronic form to the ESRC Qualidata Archive which manages preservation, access, and intellectual property aspects of data sharing.

# Ethics and regulatory issues

## LEAP intervention

The potential risks for participants using the LEAP intervention are minimal. The encouraged changes to physical activity level and dietary intake are positive and will be beneficial to all participants. The physical activity intervention promotes increasing daily physical activity through moving more and sitting less. The intervention does not promote high performance or elite exercise, where the risk of physical injury is high. The dietary intervention is intended to make changes towards a healthier eating style; it does not involve the testing of any food products, supplements or novel foods.

## HAP battery assessment

The HAP battery assessment comprises physical capability tests, questionnaires designed to assess psychological and social wellbeing, and cognitive function tests. Physical capability tests have been widely used and their compliance and acceptability is well known. These involve a minimum effort and so do not involve major risks to most participants. Qualitative process evaluation

The potential risks for participants in this research are minimal. However some participants may not wish to share some information about their personal circumstances, or provide information on the demographic data sheet. Some participants may feel uncomfortable discussing personal information within the interview. However, we will fully inform participants about the methods of data collection, and the aims and objectives of the research prior to their participation. In addition, we will take all reasonable steps to reassure participants that they should only provide information they are happy to divulge for the purposes of the research, that their information will be rendered anonymous, that participation is voluntary, that they may withdraw from the research at any time, and that they may request their data be removed from our records during the life of the study. We will also inform the participants that they may decide to withdraw themselves and their data from the qualitative process evaluation, but remain in the trial if they wish.

